### Outcomes

The primary outcome for this trial is IgE-mediated peanut and/or cashew nut allergy during infancy. In this trial, infancy is defined as birth until less than 18 months of age.

#### Allergic sensitisation to peanut/cashew nut/hazelnut/almond

The infants have skin prick testing using standard single prick lancets (Entaco distributed by Stallergenes Australia Pty Ltd) on the forearm, to determine allergen sensitisation to peanut, cashew nut, almond and hazelnut, with histamine and control solutions, in accordance with standard clinical methods. All assessment sites use the same commercially available skin prick testing extracts of peanut, cashew nut, almond and hazelnut (Greer Laboratories, USA), positive control histamine (HollisterStier, USA) and negative control 50% glycerin (Greer Laboratories, USA). Sensitisation is defined as a positive skin prick test with mean weal diameter ≥2 mm.

#### IgE-mediated peanut/cashew nut/hazelnut/almond allergy

An infant will be classified as having an IgE-mediated peanut/cashew nut/hazelnut/almond allergy if the infant has had a previous history of anaphylaxis and a positive skin prick test to the same food allergen. The Australasian Society of Clinical Immunology and Allergy (ASCIA) definition of anaphylaxis will be used for this trial: any acute onset illness with typical skin features (urticarial rash or erythema/flushing and/or angioedema), plus involvement of respiratory and/or cardiovascular and/or persistent severe gastrointestinal symptoms; or any acute onset of hypotension or bronchospasm or upper airway obstruction where anaphylaxis is considered possible, even if typical skin features are not present.^22^

Additionally, an infant will be classified as having an IgE-mediated peanut allergy without the need for a peanut food challenge if the infant has a positive skin prick test with mean weal diameter ≥8 mm to peanut.^23^ All other sensitised infants not consuming at least one teaspoon of the same nut spread (within a meal) on at least four occasions in the last 4 weeks, including at least once during the past 2 weeks, will have an in-hospital peanut/hazelnut/almond/cashew nut food challenge. Figure 2 illustrates the trial food challenge decision tree. Peanut/hazelnut/almond/cashew nut challenges with semi-logarithmic incremental doses of smooth peanut butter/hazelnut/almond/cashew nut spread given at 20 min intervals are conducted under medical supervision. Food challenges are considered positive with the occurrence of any moderate or severe dose-limiting symptoms or multiple mild symptoms following standardised scoring and stopping criteria.^24^

**Figure 2 F2:**
[figure not shown]
Nuts For Babies Study food challenge decision tree. *Nut=peanut, almond, hazelnut or cashew nut.

#### The secondary outcomes for this trial are:

IgE-mediated peanut allergy during infancy.IgE-mediated cashew nut allergy during infancy.IgE-mediated almond allergy during infancy.IgE-mediated hazelnut allergy during infancy.IgE-mediated allergy to peanut and cashew nut during infancy.IgE-mediated allergy to any two (peanut/cashew/almond/hazelnut) nuts during infancy.IgE-mediated allergy to any three (peanut/cashew/almond/hazelnut) nuts during infancy.IgE-mediated allergy to all four (peanut/cashew/almond/hazelnut) nuts during infancy.Allergic sensitisation to peanut during infancy.Allergic sensitisation to cashew nut during infancy.Allergic sensitisation to almond during infancy.Allergic sensitisation to hazelnut during infancy.Allergic sensitisation to peanut and cashew nut during infancy.Allergic sensitisation to any two (peanut/cashew/almond/hazelnut) nuts during infancy.Allergic sensitisation to any three (peanut/cashew/almond/hazelnut) nuts during infancy.Allergic sensitisation to all four (peanut/cashew/almond/hazelnut) nuts during infancy.Medical diagnosis of eczema during infancy. The assessment team nurses will ask whether the infant has had a medical diagnosis of eczema during the 6, 9 and 12-month contacts.

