### Blinding

Due to the nature of this type of dietary intervention, it is not possible to blind the participants or intervention phase research staff responsible for providing dietary advice and undertaking all participant contact phone calls during the intervention period. However, research staff undertaking the outcome assessments, all investigators and statistical analysts are blinded to intervention allocation. At each contact phone call or appointment, outcome assessors remind participants not to disclose their diet group allocation.

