**Figure 3 F3:**
[figure not shown]
Participants’ (maternal and infant) schedule of enrolment, intervention and assessment activities.

**Table 1 T1:** Baseline, intervention and follow-up data collection and assessment time-points for the participants and their infants

Data collection	Enrolment phone call: prior to birth	Phone call at 2 weeks of age	Text surveys every 2 weeks: 2 weeks to 6 months	Phone call: 3 months	Phone call: 6 months	Monthly text surveys: 7–11 months	Phone call: 9 months	Infant final assessment: 11–18 months
Baseline data and randomisation	X							
Intervention period		X	X	X	X			
Birth details		X						
Maternal diet compliance		X	X	X	X			
Infant feeding		X	X	X	X	X	X	X
Hospitalisation				X	X		X	X
Follow-up Period					X	X	X	X
Infant eczema				X	X		X	X
Infant peanut and cashew nut spread intake						X	X	X
Nut allergic sensitisation								X
Peanut and/or cashew nut allergy (primary outcome)								X

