#### Final assessment at 11–18 months of age

Participants are asked to attend an appointment at the major paediatric hospital in each state: Perth Children’s Hospital (Perth, Western Australia) and Royal Children’s Hospital (Melbourne, Victoria). If the participant is unable to attend this appointment in-person, assessment research staff will contact them via telephone. The participants are asked questions about breastfeeding, any infant consumption of peanut butter, cashew nut, hazelnut and almond spread, any suspected infant allergic reactions to peanut, cashew nut, hazelnut and almond, and whether their infant has had a medical diagnosis of eczema, use of any eczema treatments, any maternal and/or infant hospitalisations and past month total household consumption of peanuts, cashew nuts, almonds and hazelnuts (and their associated nut spreads). Participating infants have skin prick testing (as described in the Outcomes section), and a food challenge if required (as described in the Outcomes section).

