### Data collection, management and monitoring

Data are collected by trained research staff at each participating site and entered directly into a trial-specific REDCap database with defined user-level access to facilitate trial management, data collection and blinding as appropriate. A record of all potential participants successfully screened for eligibility and consented is recorded in real time. Once consented and randomised, the REDCap database automatically calculates study milestones for each participant. This information is readily available for research staff to enable scheduling of appointments and phone calls. The trial-specific REDCap database has inbuilt data entry validity checks to ensure immediate resolution of data queries. Data queries are also generated by statisticians during regular blinded reviews of data quality. Electronic data are stored on secure servers with access only granted to authorised study personnel. All data collected are treated with confidence. Data entered by individual study sites are routinely monitored by the clinical trial coordinators to check protocol adherence and study progress. Monthly summary reports are generated, including screening data, enrolment, phone call and appointment completions, and reviewed at trial investigator meetings. Site monitoring to ensure compliance with good clinical practice and the study protocol are conducted at site start-up and then 6 monthly or as required to ensure the integrity of the trial. The trial investigators and The Kids Research Institute Australia (sponsor) will permit trial-related monitoring, audits and regulatory inspections, providing direct access to source data/documents to the approving Human Research Ethics Committee and Institutional Governance review bodies. The trial chief investigator team will review and make protocol amendments if required, monitor overall study progress and make decisions regarding resource allocation at monthly online meetings.

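### The protocol contradicts itself on whether blinded or unblinded staff make the 6-month call, which collects both maternal diet compliance and infant eczema

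*Protocol article*

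**What the plan says.** The protocol article's Blinding section states that "research staff undertaking the outcome assessments, all investigators and statistical analysts are blinded to intervention allocation". It accepts that participants cannot be blinded, and neither can the "intervention phase research staff responsible for providing dietary advice and undertaking all participant contact phone calls during the intervention period". As a safeguard, "outcome assessors remind participants not to disclose their diet group allocation".

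Under the secondary outcomes, eczema is ascertained as follows: "The assessment team nurses will ask whether the infant has had a medical diagnosis of eczema during the 6, 9 and 12-month contacts".

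In Table 1, the row "Maternal diet compliance" is marked at the 2-week call, the two-weekly text surveys, the 3-month call and the 6-month call. The infant eczema row is marked at the 3-, 6- and 9-month calls and at the final assessment. The 6-month call is marked as both intervention period and follow-up period.

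The section on the 6- and 9-month calls lists infant feeding, infant nut-spread intake, suspected reactions to the four nuts, eczema and hospital admissions. It lists no question on the mother's own nut intake, and it treats 6 months as the close of the intervention.

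At the final assessment the family is asked about "past month total household consumption of peanuts, cashew nuts, almonds and hazelnuts (and their associated nut spreads"). The infant has skin prick testing, and a food challenge if required, at the same assessment.

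**The concern.** Participants know their diet, so the trial relies on the blinding of those who collect and judge outcomes. The article presents this among its strengths. A mother's reported intake comes close to a statement of her arm: the high group is asked for 60 or more peanuts and 40 or more cashews a week, and the low group is capped at 20 and 12. Whoever takes the compliance answer from an adherent mother can usually tell the arm.

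The 6-month call carries that answer together with two infant items that matter for outcomes. One is eczema, a secondary outcome. The other is suspected nut reactions. Under the unscheduled-visit section, a reported reaction leads to a study-doctor call and possibly an early skin test. Under the allergy definition, a history of anaphylaxis with a positive skin test classifies the infant as allergic. How this call is staffed therefore also touches a step that feeds the primary outcome.

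**Working it through.** No figure in the protocol bears on this point, so the check sets the sections side by side.

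| Section | What it implies for the 6-month call |
|---|---|
| Blinding | Unblinded staff are "undertaking all participant contact phone calls during the intervention period" |
| Table 1 | The call lies in the intervention period and also in follow-up; compliance and eczema are both due |
| Secondary outcomes | Blinded assessment nurses ask about eczema |
| At 6 and 9 months postnatal | Infant items only; no maternal intake question |

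Three readings are possible.

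1. **One assessor makes the whole call.** If Table 1 is followed, a blinded nurse hears the mother's intake. This also contradicts the Blinding section, which gives all such calls to the other team.
2. **One intervention-team member makes the whole call.** Eczema and suspected reactions are then collected unblinded. This contradicts the eczema definition.
3. **Two teams share the contact.** The double marking in Table 1 is compatible with a handover, but no section says so, and it conflicts with the word all in the Blinding section.

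No reading satisfies all four sections as printed.

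**Eczema contacts.** The definition names 6, 9 and 12 months. Table 1 has 3, 6 and 9 months and a final assessment at 11–18 months. Two differences follow: Table 1 has no 12-month contact, and the definition omits the 3-month answer that Table 1 collects. The 3-month call falls within the intervention period, so by the Blinding section that answer is taken by unblinded staff. The 3-month section also has household nut quantities asked in the same call.

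**Final visit.** The allocated diet ends at 6 months. The gap to the final assessment runs from 11 − 6 = 5 months to 18 − 6 = 12 months. The question covers the past month and the whole household, so it does not measure the allocated diet. It could still point to the arm if habits persist. It also covers almonds, which the control group is encouraged to eat as a substitute snack. The document gives no data on persistence. It does not state whether the question comes before or after the skin test, or whether the interviewer also reads the weals.

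**The case against.** The strongest reply is that the 6-month problem is loose drafting. The description of that call has no maternal intake question, whereas the 3-month description does list household quantities. Table 1 also marks compliance at the 2-week call, where the text mentions only whether the mother has questions about her diet. The two-weekly text survey already captures intake up to 6 months. Eczema is a parent-reported medical diagnosis, and the parent is unblinded whoever asks. Much of this stands. It shows that the protocol may be run properly in practice, and it limits the possible harm to eczema. It does not remove the conflict over who makes the call, and it makes the repair easier.

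Three stronger inferences are tempting, and the document does not support them.

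- *Intake data unblind the statisticians.* The article says "Data queries are also generated by statisticians during regular blinded reviews of data quality", describes user-level database access with blinding as one purpose, and has analysts fully blinded until database lock. Nothing says that intake fields are shown to them. Who derives the per-protocol set can properly be left to the analysis plan, which is not at hand.
- *The final visit unblinds the assessors.* A past-month household figure, taken 5 to 12 months after the diet ended, can at most hint at the arm. Both groups have by then been advised on introducing the nut spreads to the infant. Testing materials are common to all sites and challenge scoring is standardised, which gives some further protection.
- *A biased relative risk can be put on the primary outcome.* Any such figure would simply restate an assumed misclassification rate, for an outcome where no unblinding is shown.

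**Conclusion.** The contradiction over the 6-month call is real. The stated assessor blinding and the printed schedule cannot both be followed for that contact. The outcome directly affected is eczema. Suspected-reaction reports are affected too, as an upstream step towards the allergy classification. The final-visit question is a lesser route and matters only on the assumption, untested in the document, that household habits outlast the intervention. The mismatch between the eczema definition and Table 1 is a separate and definite inconsistency.

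The size cannot be expressed as a number. The document shows an avoidable route by which blinding could fail. It does not show that an assessor learns the allocation, or that any outcome is biased. The point is worth acting on because assessor blinding is a property the trial relies on and the corrections cost very little.

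**What to change.** 1. **6-month call.** Collect maternal compliance only through the existing text survey or by the intervention team. Limit the assessment team's 6-month script to infant items. Reconcile the Blinding section, the eczema definition, Table 1 and the description of the 6- and 9-month calls, so that they name the team responsible for compliance, eczema and suspected reactions.
2. **Final assessment.** Ask the household-consumption question only after skin-test and any challenge results have been recorded, or move it to a self-completed survey link of the kind already in use.
3. **Eczema definition.** Replace the 12-month contact with the 11–18-month final assessment. State whether the 3-month answer, which unblinded staff collect, counts towards the outcome.

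The cost is a revision of call scripts, question order and protocol wording. The survey option in item 2 needs one further survey link, because the monthly surveys stop at 11 months. No new data item, visit or staff member is needed. Recruitment is expected to continue until December 2027, so the changes can be made while the trial is running.

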### Participant timeline

Figure 3 illustrates the participants’ schedule of enrolment, intervention and assessment activities, and table 1 summarises the baseline, intervention and follow-up data collection and assessment time-points.

**Figure 3 F3:**
[figure not shown]
Participants’ (maternal and infant) schedule of enrolment, intervention and assessment activities.

**Table 1 T1:** Baseline, intervention and follow-up data collection and assessment time-points for the participants and their infants

Data collection	Enrolment phone call: prior to birth	Phone call at 2 weeks of age	Text surveys every 2 weeks: 2 weeks to 6 months	Phone call: 3 months	Phone call: 6 months	Monthly text surveys: 7–11 months	Phone call: 9 months	Infant final assessment: 11–18 months
Baseline data and randomisation	X							
Intervention period		X	X	X	X			
Birth details		X						
Maternal diet compliance		X	X	X	X			
Infant feeding		X	X	X	X	X	X	X
Hospitalisation				X	X		X	X
Follow-up Period					X	X	X	X
Infant eczema				X	X		X	X
Infant peanut and cashew nut spread intake						X	X	X
Nut allergic sensitisation								X
Peanut and/or cashew nut allergy (primary outcome)								X

#### Baseline screening and data collection

Eligibility is confirmed and demographic information collected according to CONSORT guidelines.^20^ For eligible participants, written informed consent is obtained prior to the birth of the infant (from 35 weeks’ gestation onwards).

Baseline data are recorded, including maternal age, education, ethnicity, height, prepregnancy weight, primiparous or multiparous, any infants previously breastfed, parental and/or sibling (of the infant) allergic disease(s) history, any pets, and usual (past month) total household intake of peanuts, peanut butter, cashew nuts and/or cashew nut spread.

#### Two weeks postnatal

Participants are phoned to collect details on infant sex, birth weight, length and head circumference, birth gestation, birth mode, breastfeeding status, any infant formula use, and asked if they have any questions about their assigned nut diet.

#### At 3 months postnatal

Participants are phoned and asked if they have any study-related questions. Information about breastfeeding and any infant formula use is collected. Participants are also asked about any maternal or infant hospital admissions since birth, if their infant has had a medical diagnosis of eczema, and quantities of peanuts, cashew nuts, almonds and hazelnuts (and associated nut spreads) that all members of their household have eaten over the previous month.

#### At 6 and 9 months postnatal

Participants are phoned and asked questions about breastfeeding, solid foods introduction, infant consumption of peanut butter, almond, hazelnut and cashew nut spread, any suspected allergic reactions in infants to peanut/cashew nut/almond/hazelnut, any medical diagnosis of infant eczema, and any maternal or infant hospitalisations. At 6 months (end of intervention period), all participants (both groups) are provided with advice on the introduction of peanut, cashew nut, almond and hazelnut spreads in the infant diet. All families are educated on recognising the signs and symptoms of an allergic reaction and advised what to do in such circumstances.

#### At 7, 8, 10 and 11 months postnatal

Participants are sent a link via mobile phone to complete a short survey to capture age of introduction of peanut butter and cashew nut spread, how much peanut butter and cashew nut spread their infant has eaten over the previous week (once introduced) and to report any suspected allergic reactions to peanut or cashew nut.

#### Final assessment at 11–18 months of age

Participants are asked to attend an appointment at the major paediatric hospital in each state: Perth Children’s Hospital (Perth, Western Australia) and Royal Children’s Hospital (Melbourne, Victoria). If the participant is unable to attend this appointment in-person, assessment research staff will contact them via telephone. The participants are asked questions about breastfeeding, any infant consumption of peanut butter, cashew nut, hazelnut and almond spread, any suspected infant allergic reactions to peanut, cashew nut, hazelnut and almond, and whether their infant has had a medical diagnosis of eczema, use of any eczema treatments, any maternal and/or infant hospitalisations and past month total household consumption of peanuts, cashew nuts, almonds and hazelnuts (and their associated nut spreads). Participating infants have skin prick testing (as described in the Outcomes section), and a food challenge if required (as described in the Outcomes section).

#### Unscheduled visit prior to 11 months of age

If a parent reports that their infant has had an allergic reaction to peanut/cashew nut/almond/hazelnut spread prior to 11 months of age, they will be telephoned by a study doctor. The study doctor will advise either that the parent can continue to offer the nut spread to the infant, or they will be asked to attend for skin prick testing and assessment. At this unscheduled visit, the infant will only be skin prick tested to the nut that their parent has reported their allergic reaction to. The infant will still attend the final assessment between 11 and 18 months of age to undergo skin prick testing to the other nuts. If at the unscheduled visit prior to 11 months of age the infant has a positive skin prick test with mean weal diameter ≥2 mm, the food challenge decision tree (figure 2) will be followed.

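### As worded, an infant found negative to a nut at an unscheduled visit before 11 months is not retested to that nut at the final assessment, so allergy to it developing in between would go uncounted

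*Protocol article*

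**What the plan says.** All references are to the protocol article.

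- **Unscheduled visit prior to 11 months of age.** A parent's report of a reaction leads to a call from a study doctor, who may ask for a visit. There, "the infant will only be skin prick tested to the nut that their parent has reported their allergic reaction to". Afterwards: "The infant will still attend the final assessment between 11 and 18 months of age to undergo skin prick testing to the other nuts". The next step is given only for a positive early result: if "the infant has a positive skin prick test with mean weal diameter ≥2 mm, the food challenge decision tree (figure 2) will be followed". Nothing is said about repeating the test after a negative result.
- **Outcomes.** The primary outcome is IgE-mediated peanut and/or cashew allergy during infancy. "In this trial, infancy is defined as birth until less than 18 months of age".
- **IgE-mediated peanut/cashew nut/hazelnut/almond allergy.** There are three routes to classification. The first requires that "the infant has had a previous history of anaphylaxis and a positive skin prick test to the same food allergen". The second, for peanut only, is a weal of at least 8 mm. The third is a positive food challenge, offered to "All other sensitised infants not consuming at least one teaspoon of the same nut spread" on a stated recent schedule. Sensitisation is itself a skin prick result of at least 2 mm.
- **Final assessment at 11–18 months of age.** Parents are asked about "any suspected infant allergic reactions to peanut, cashew nut, hazelnut and almond", and infants have skin prick testing as set out under Outcomes, which names all four nuts.

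**The concern.** Limiting the final test to the remaining nuts makes sense for an infant already classified as allergic at the early visit. It does not suit an infant whose early result was negative. That infant's status for the reported nut is settled before 11 months, while the outcome window runs to just under 18 months.

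These infants have had a suspected reaction that a study doctor thought worth testing, so they are a natural place to look for later allergy. For peanut or cashew, a case that develops after the early visit would be missing from the primary outcome. For any of the four nuts, the sensitisation outcomes would mix results from before 11 months with results at 11–18 months. No later analysis can recover a test that was not done.

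**Working it through.** **1. Following one infant through the text.** Suppose an infant has a peanut weal below 2 mm at an unscheduled visit at 8 months, anaphylaxis to peanut at 13 months, and a final assessment at 14 months (illustrative ages).

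- Anaphylaxis route: the history is reported at the final assessment, but a positive peanut skin prick test is also required. The only peanut test was negative.
- Weal of at least 8 mm: no peanut test is provided for at 14 months.
- Challenge route: open only to sensitised infants, and the only result on file is below 2 mm.

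No route classifies this infant as peanut allergic. Another unscheduled visit does not help, because that pathway covers reactions before 11 months.

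The gap is clearest for a weal below 2 mm. An infant who was skin prick positive but passed an early challenge does have a positive test on file. The text does not say whether that test would support a later anaphylaxis history or a second challenge. It provides no new skin prick test for this infant either.

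**2. The time at issue.** The right measure is the interval from the unscheduled visit to the infant's own final assessment. A visit at 10 months and an assessment at 11 months gives 11 − 10 = 1 month; the example above gives 14 − 8 = 6 months. Measuring to the end of the window would overstate the gap, since any infant assessed at 11 months has up to 18 − 11 = 7 untested months.

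**3. The plan's own sample size.** Inputs from Sample size: p1 = 0.031, p2 = 0.0155, alpha 0.05, power 90%. The two-sided test is from Data analysis plan. With pooled variance under the null and p̄ = 0.02325:

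n = [1.960 × √(2 × 0.02325 × 0.97675) + 1.2816 × √(0.031 × 0.969 + 0.0155 × 0.9845)]² / 0.0155²
= [1.960 × 0.2131 + 1.2816 × 0.2128]² / 0.00024025, which rounds up to 1985 per group.

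This matches the plan. Allowing for 10% loss, 1985 / 0.90 gives 2206 per group and 4412 in total, as stated.

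**4. Effect of missed cases.** Expected cases are 1985 × 0.031 = 61.5 and 1985 × 0.0155 = 30.8, total 92.3. The documents do not give the share missed, so it is an assumption (m), taken as equal in both arms:

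| m (assumed) | Cases missed (92.3 × m) | Relative risk | Power at 1985 per group |
|---|---|---|---|
| 0% | 0 | 0.50 | 90.0% |
| 1% | 0.9 | 0.50 | 89.7% |
| 2% | 1.8 | 0.50 | 89.4% |
| 5% | 4.6 | 0.50 | 88.5% |
| 10% | 9.2 | 0.50 | 86.7% |

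The relative risk is unchanged because (1 − m) cancels: 0.0155(1 − m) / [0.031(1 − m)] = 0.50.

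**The case against.** **No explicit ban on retesting.** The sentence about the early visit contains a restriction to one nut; the sentence about the final assessment does not. It can be read as explaining why the infant must still attend, and the general text on the final assessment points to a four-nut panel. Staff who heard of a recent peanut anaphylaxis might well add peanut. This stands in part: not retesting is the plain implication, not a stated prohibition. But the specific sentence governs these infants, and its wording has no natural reading that includes the nut already tested. If the two sections are thought to conflict, sites could act differently, and the wording still needs fixing.

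**Detail may lie elsewhere.** The decision tree figure and the full protocol are not visible. However, the article invokes the tree at this visit only after a positive test, and what it states about the final assessment is a definite procedure.

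**The effect is small.** This stands. A telephone screen by the study doctor limits the number of early tests. The primary outcome is peanut and/or cashew, so some missed infants are still counted through the other nut; the plan itself takes 16.7% of peanut-allergic infants to be cashew allergic too.

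**Stronger readings the documents do not support.**

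- A reader might infer that these are the only infants left untested at the final assessment. They are not: families unable to attend are contacted by telephone.
- A reader might infer bias between arms, because early testing starts with a parent's report and, under Blinding, "it is not possible to blind the participants". Nothing in the documents shows that reports, or negative early tests, would differ by arm. Even if 1% of cases were missed in one arm and 5% in the other (pure assumption), the relative risk would read 0.50 × 0.95/0.99 = 0.480 or 0.50 × 0.99/0.95 = 0.521.

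**Conclusion.** The point holds as a gap in the wording. As written, an infant with a negative early result has no further skin prick test to the reported nut. Allergy to that nut developing before the infant's own final assessment would then go uncounted, most clearly when the early weal was below 2 mm. Sensitisation to that nut is also measured at a younger age than in other infants.

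The size cannot be derived from the documents and is probably small. On an assumed equal loss of 1% to 10% of cases, power falls by 0.3 to 3.3 percentage points and the relative risk does not move. The conclusion rests on reading the unscheduled-visit section as the rule for these infants, with the decision tree figure and full protocol unseen. Severity: minor; a cheap improvement.

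**What to change.** In the section on the unscheduled visit, replace *the other nuts* with *all four nuts, except any nut to which the infant has already been classified as allergic*. Follow the decision tree on the new result, and count the infant as allergic if either visit meets the existing definition.

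The cost is one extra skin prick per affected infant at a visit already scheduled, plus a few added food challenges. No visit is added and the outcome definition does not change. The change can still reach most of the trial: recruitment is expected to run to December 2027 and final assessments to March 2029. It cannot recover the test for infants whose final assessment is already complete.
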